## Abstract

**Background:**

The longitudinal study, “Couples Lived Experiences,” focuses on whether and how relationship characteristics of older couples change with the cognitive decline of one member of the couple, and how these changes affect each individual’s emotional and physical health outcomes. Until now, most psychosocial research in dementia has focused either on the person with dementia (PWD) or the caregiver separately. The previous literature examining relationship characteristics and their role in outcomes for the caregiver and PWD is scant and suffers from methodological issues that limit the understanding of which relationship characteristics most influence outcomes for caregivers and care-receivers and what other factors may mitigate or exacerbate their effects.

**Methods:**

We will enroll 300 dyads and collect information via online interviews of each member of the couple, every 6 months for 3 years. Relationship characteristics will be measured with a set of short, well-validated, and reliable self-report measures, plus the newly developed “Partnership Approach Questionnaire.” Outcomes include global quality of life, subjective physical health, mental health (depression and anxiety), and status change (transitions in levels of care; i.e., placement in a nursing home). Longitudinal data will be used to investigate how relationship characteristics are affected by cognitive, functional, and behavioral changes, and the impact of these changes on health outcomes. Qualitative data will also be collected to enrich the interpretation of results of quantitative analyses.

**Discussion:**

Psychosocial interventions have demonstrated effectiveness in promoting the wellbeing of PWD and their caregivers. The knowledge gained from this study can lead to the development or enhancement of targeted interventions for older couples that consider the impact of cognitive and functional decline on the relationship between members of a couple and thereby improve their wellbeing.

**Trial registration:**

This study has been registered with ClinicalTrials.gov. ClinicalTrials.gov Identifier is: NCT04863495.

## Background

As the population continues to age, there is a corresponding increase in the number of people with Alzheimer’s disease and related dementias (ADRD) [1, 2] and the number of family caregivers. While funding for the development of novel pharmacological and disease-modifying targets often takes center stage [3, 4], to date, none has been identified that can substantially modify the disease course. Meanwhile, the financial and emotional cost to patients and families and the cost to the federal health care budget continue to grow.

Psychosocial interventions have substantial evidence of efficacy in improving outcomes for caregivers and persons with dementia (PWD) (e.g., the NYU Caregiver Intervention (NYUCI) [5–8]. The health outcomes demonstrated by the NYUCI are largely mediated by social support [9]; Moreover, many large-scale epidemiologic studies corroborate this finding and demonstrate that social support can predict better health outcomes and reduce the risk for premature mortality [10].

Partner relationships may be a particularly important form of social support, which is why the current study focuses on relationship characteristics of couples. In facing a chronic illness, both partners need support, and each is generally the primary support of the other [11]. Spouses frequently share stressors appraising them as “ours” rather than “mine”, pool resources, and actively engage in joint coping efforts [12]. Cross-sectional and longitudinal studies have documented concordance in levels and changes in spouses’ mental health and wellbeing. For example, in a longitudinal analysis of a repeated household survey, one partner’s mental health status predicted about 25% of the variance in the other partner’s mental health [13]. Older adults, whose relationships are generally of greater duration, were likely to have a higher concordance, which may reflect dynamic processes and shared experiences that increase with the length of the marriage [14]. The burden of dementia on older couples is especially poignant, and although they generally endure the illness together, cognitive decline and behavioral symptoms alter the role of the partner-caregiver and impact their relationship in ways this study aims to elucidate.

The stress process model [15] suggests that caregiver wellbeing is affected not only by primary stressors originating directly from illness and care of the patient but also from secondary stressors (such as family conflict and constriction of social activities). Social support and appraisal of the meaning of the stressors can mediate the effects of primary caregiving stressors on caregiver wellbeing [16]. In the early 1990s, the growing awareness of the impact of illnesses such as ADRD on the quality of the marital relationship led to an extension of the stress process paradigm to include a concept that was defined as dyadic coping, a process which includes the stress signals of one partner, the perception of the signals by the other partner, and the reaction of the other partner [17]. This extended version of the stress process paradigm provides a conceptual motivation for our choice of measures.

The primary goal of the current study is to further our understanding of the impact of relationship characteristics on outcomes for the caregiver and care-recipient in spousal or partner dyads affected by cognitive decline. This goal will be pursued through three specific aims: 1) to determine the cross-sectional association between dyadic relationships and health outcomes; 2) to evaluate the change in the couple’s relationship over time, the potential causative factors, and the implications this change holds for the wellbeing of each member of the couple, and 3) to use qualitative data collection and analysis to further explore the personal impact of changes in the relationship and enhance the interpretation of the results of the quantitative analyses.

### Limitations to prior research

The body of literature examining relationship characteristics and their role in outcomes for the caregiver and care-recipient is scant and suffers from methodological issues that limit our ability to understand which relationship characteristics most influence outcomes for caregivers and care-recipients and what other factors may mitigate or exacerbate their effects. Although many studies look at relationship characteristics and their association with outcomes for caregivers and PWD cross-sectionally, we are not aware of any study that has examined changes in multiple aspects of relationship characteristics that occur over the course of the illness and how those changes impact health outcomes. Further, most of the studies that explore relationship characteristics do so only from the caregiver’s perspective [18], or rely on ratings made on behalf of the PWD by the caregiver, another family member, or friend, as once he or she has dementia, even in the early stage, the PWD had been viewed as no longer being a reliable reporter [18, 19]. Our review of the literature suggests that other limitations to prior research on relationship characteristics and dementia outcomes include small sample sizes, and unexamined potential confounds that limit the interpretation of the importance of relationship factors.

There is a wealth of literature on the impact of caregiver factors and care-recipient factors on outcomes, mostly from the perspective of the caregiver [20]. The caregiving literature explores how factors such as social support, self-efficacy, and positive aspects of caregiving impact mental and physical health outcomes for caregivers, and transitions to residential care. The literature is also robust when considering how outcomes are affected by care recipient factors such as disease characteristics (cognitive and functional decline, neuropsychiatric symptoms). However, most clinicians would agree that the relationship itself, as separate from factors specific to each individual in the dyad, has the potential to contribute to outcomes.

### Rationale for this study

A longitudinal study of dyads living with dementia is essential to understanding how relationship characteristics change over time and contribute to health outcomes for caregivers and care-recipients. In this study, we will focus on relationship characteristics and their effect on mental and emotional health outcomes for each individual in the dyad. The dyadic nature of this study will yield information about the relationship from the perspective of both members of the dyad. The primary goal is to understand the relationship between the members of a couple over time, how it changes as one becomes cognitively, functionally, and behaviorally impaired, and how the changes in their relationship affect the wellbeing of each of them. We will assess *both* members of the dyad at varying stages of the disease, from normal through early dementia to get information on their relationship, and how it changes from *both* their perspectives.

By collecting longitudinal data on caregiver factors, care-recipient factors and relationship factors, we will be able to determine how relationship factors contribute to the caregiver and care-recipient outcomes above and beyond the well-studied individual factors. We will investigate how relationship characteristics change over time as cognitive, functional, and behavioral problems increase, and the impact of these changes on outcomes such as global quality of life, subjective physical health, mental health (depression), and the amount of time to care transitions (for example, placement in a nursing home). Qualitative data collection and analysis will be used to further explore the dynamic nature of the relationship characteristics of interest and enhance the interpretation of the results of quantitative analyses.

## Methods

### Overview

We will enroll a total of 300 couples over an 18-month period, recruited from two locations (the New York City, New York metropolitan area and the Boston, Massachusetts metropolitan area), with 150 dyads per site. Among these couples we will recruit 60 dyads in which both members have normal cognition, 140 in which one member has Mild Cognitive Impairment (MCI), and 100 in which one member has ADRD in the early stages. Information about the study will be distributed through channels such as memory clinics, trial registries and community organizations that serve older adults. While we had originally planned to conduct the assessments in person, the exigencies of the COVID pandemic necessitated changing the protocol so that all interviews will be conducted via video conferencing.

Both members of the dyad will be asked to complete an eligibility screen and provide consent to participate via an online portal. Structured self-report instruments will be administered at baseline and at 6-month intervals over a 3-year period to obtain each of their perspectives on changes in multiple aspects of their relationship. We will characterize participants throughout the study at each time point into one of three groups (normal, MCI, and ADRD) based on cognitive performance using the MoCA [21] combined with activities of daily living assessment scores using the FAQ [22] to capture decline from normal to MCI to ADRD. The assessment will be completed by both members of the dyad from normal through early dementia. If at the conclusion of a follow-up interview the participant is deemed to no longer have capacity, the data from that assessment will be excluded from analyses and the participant will not be included in further assessments. We will continue to evaluate the relationship from the caregiver’s perspective when a capacity evaluation determines that the person with dementia can no longer be a reliable respondent. If one member of a couple dies, the other member will be asked to complete an exit bereavement assessment 6 months after the death.

The baseline assessment includes measures of relationship style and potential outcomes such as depression and physical health. We will use these cross-sectional data to develop an initial statistical model which will include exogenous factors, primary stressors, mediators and outcomes (Aim 1) which can be tested in longitudinal analysis. The longitudinal study will enable us to assess the validity of this model and modify it to reflect the additional information about changes in relationships over time in response to cognitive decline in one member of the couple and the impact of these changes on health outcomes of both members of the couple (Aim 2).

In addition to the quantitative study, we will hold focus groups with 32 of these couples (16 per site) after the last 6-month follow-up (3 years after the baseline assessment). A qualitative examination using the results of these focus groups will complement the longitudinal analysis by illuminating interpersonal processes by which change or continuity in relationship and couples’ wellbeing occurs (Aim 3). Qualitative analysis will also provide an understanding of the relevance of the constructs identified via the longitudinal analysis as they apply to individual members of dyads’ experience of their relationship as it was and as it is now. Figure 1 contains a schematic of the above delineated protocol.

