### Assessment

#### Process

Assessments will be conducted via videoconferencing, using a HIPPA-compliant video-conferencing platform. Each participant will complete the assessments separately from his or her partner. The assessments will be administered by a research coordinator verbally, with visual cues shared on screen for certain instruments when necessary. The assessment process will be consistent and standardized at both sites and for all interviewers. We anticipate that it will take couples an average of 2 h at baseline and 1.5 h at follow-up to complete the assessments, based on the results of a pilot of the battery with eight older individuals who completed it in as little as 40 min and no more than 1 h.

We will collect data from each member of the couple that includes demographic characteristics, psychosocial attributes (e.g., perceived social support, self-efficacy), relationship factors (relationship satisfaction, relationship continuity, partnership approach) and outcomes, including global quality of life, physical health, mental health (depression and anxiety) and status change (for example, placement outside the home). This assessment battery will enable us to estimate the contribution of relationship factors, above and beyond the commonly well-studied individual factors, to caregiver and care-recipient outcomes.

For couples in which one participant identifies as the caregiver of the other, we will use additional instruments to measure caregiver responses to the effects of cognitive changes (e.g., loss of intimate exchange, ability to identify positive aspects of caregiving) and care-recipient attributes (i.e., functional ability and behavioral problems from the perspective of the caregiver). It should be noted that, if one member of the couple declines in cognitive function and the other doesn’t identify as a caregiver, the caregiver battery will not be used.

At each follow-up visit, the same procedure used during the intake visit will be followed. As the individuals with cognitive impairment or ADRD progress in the severity of their symptoms, they will continue in the study until scoring 12 or less on the MoCA or are deemed to lack capacity, after which they will be withdrawn from the study; their study partner will continue to participate.

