Life Orientation [30]: This 10-item assessment of feelings of generalized optimism vs pessimism, rated on a 5-point scale ranging from “I agree a lot” to “I disagree a lot”.

Meaning and Purpose in Life [31]: This 18-item measure of life purpose rated on a 5-point Likert scale from Strongly Disagree to Strongly Agree.

Coping self-efficacy [32]: This 10-item questionnaire assessing feeling of self-efficacy in daily activities, rated on a 5-point Likert scale with “1 = Never” and “5= Very Often”.

Geriatric Depression Scale [33]: This 15-item measure of symptoms of depression among older adults; 15 ‘yes’ or ‘no’ questions in which participants respond in reference to how they felt over the past week.

Beck Anxiety Inventory (BAI) [34]: This 21-item measure of symptoms of anxiety during the past month on a 4-point scale from “Not at all” to “Severely-it bothered me a lot.”

Physical Health Questionnaire [35]: This measure includes three global self-rated physical health items from the OARS battery of questionnaires (ICC = 0.83) to assess subjective evaluation of health The sum of the 3 questions is used to measure SRH.

Sleep Survey: This measure includes two items to assess subjective sleep quality over the previous month.

EuroQol Questionnaire Global Quality of Life [36]: This measure assesses overall quality of life on a scale of 0–100 with “100 being the best quality of life imaginable”.

Caregiver Screener: Once all of the above questionnaires are completed, all individuals will be administered a short Caregiver Screener which asks if individuals identify as a caregiver, if their care partner needs additional help with tasks, how often they provide care, and utilization of outside resources to assist in caring for their partner. The screener determines whether additional questionnaires should be implemented with the caregiving partner.

*Functional Activities Questionnaire [22]: This 10-item measure to assess the abilities of the person with dementia. Each functional activity assessed as: (3) Dependent; (2) Requires assistance; (1) Has difficulty but does by self; (0) Normal or (0) Never did [the activity] but could do now; (1) Never did and would have difficulty now.

*Revised Memory and Behavior Checklist [37]: This 24-item measure assesses the functioning and behavior of an individual with dementia. Caregivers are asked if a certain behavior is present and if so how much it bothers them, on a scale from “Not at all” to “Extremely.”

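### Grouping at every visit needs the FAQ, but on the clearest reading the FAQ is collected only when a partner identifies as caregiver, so the functional half of the rule is missing, possibly selectively

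*Protocol article*

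**What the plan says.** **The grouping rule.** Methods, Overview: "We will characterize participants throughout the study at each time point into one of three groups (normal, MCI, and ADRD"), and this is done "based on cognitive performance using the MoCA [21] combined with activities of daily living assessment scores using the FAQ [22"]. The stated purpose is to capture decline across the three groups. Planned enrolment is "60 dyads in which both members have normal cognition, 140 in which one member has Mild Cognitive Impairment (MCI), and 100" with early ADRD.

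**Who gets the MoCA.** Assessment battery: all participants, at the end of every interview.

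**Who gets the FAQ.** Process describes additional instruments for couples in which one member identifies as the other's caregiver. Among them are care-recipient attributes, namely "functional ability and behavioral problems from the perspective of the caregiver". It then says that if one member declines cognitively and the other does not "identify as a caregiver, the caregiver battery will not be used". In Assessment battery, the Caregiver Screener comes after the common questionnaires: "The screener determines whether additional questionnaires should be implemented with the caregiving partner". The next entry, marked with an asterisk, is the "Functional Activities Questionnaire [22]: This 10-item measure to assess the abilities of the person with dementia".

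**Wording that points the other way.** Assessment battery opens by saying that all participants complete the listed battery at baseline. It closes by carrying the listed questionnaires into all follow-up visits with three named exceptions, and the FAQ is not one of them.

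**Relationship continuity.** Process lists "relationship factors (relationship satisfaction, relationship continuity, partnership approach") among data from each member of the couple. Assessment battery gives the continuity measure an asterisk and describes it as the caregiver's appraisal.

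**The concern.** The grouping rule has two components, and the plan appears to collect one of them only in a self-selected part of the sample. The gate closes in a situation the rule is meant to detect: a member declines and the partner has not taken on the caregiver label.

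Group is central to the analysis. Aim 1 is stratified by cognitive function and uses multinomial regression on group. Aim 2 tests a group-by-time interaction. The Rationale also names functional impairment as one of the changes whose effect on the relationship is to be studied.

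The gap may not be random. The Discussion says that people in the caregiving role do not always see themselves as caregivers, and that this variation may be explained by characteristics of the two members that the study is investigating. Whether function is recorded, and so how a couple is grouped, could then depend on the predictors of interest. The section on attrition and sensitivity analysis deals with dropout and does not cover this gap.

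**Working it through.** The plan states no figure for FAQ coverage, so there is none to reproduce. The check has two parts.

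**1. Is the FAQ gated?**

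- For the gate: Process places caregiver-rated function among the conditional instruments. The FAQ is the only functional measure in the list that fits that description.
- For the gate: the FAQ follows directly after the screener and shares its asterisk with scales that only a caregiver can answer, such as the Positive Aspects of Caregiving Scale. The paragraph on changed living arrangements qualifies another starred scale, the behaviour checklist, as applying if the respondent is a caregiver.
- Against the gate: the opening and closing sentences of Assessment battery, as above. Taken literally, they would also give the caregiver-only scales to everyone, which Process rules out.
- The asterisk has no legend in the text at hand, and no sentence names the FAQ as withheld.

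The gated reading is therefore the clearer one, but the sections conflict. The article gives no other scale of daily activities and no rule for grouping someone without an FAQ score.

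**2. How many couples would lack it?**

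Inputs from Overview: 60 normal + 140 MCI + 100 ADRD = 300 dyads. Assumed, because the documents give no rate: nobody identifies as caregiver in the normal dyads, and shares p(MCI) and p(ADRD) of partners identify in the other two groups.

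Couples without FAQ = 300 − [60 × 0 + 140 × p(MCI) + 100 × p(ADRD)]

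| p(MCI) | p(ADRD) | With FAQ | Without, of 300 | Without, of the 240 MCI and ADRD dyads |
|---|---|---|---|---|
| 100% | 100% | 140 + 100 = 240 | 60 (20%) | 0 |
| 50% | 90% | 70 + 90 = 160 | 140 (47%) | 80 |
| 30% | 70% | 42 + 70 = 112 | 188 (63%) | 128 |
| 10% | 50% | 14 + 50 = 64 | 236 (79%) | 176 |

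The last column is the one that bears on the MCI/ADRD boundary. The 60 normal dyads add to every total, but the loss there concerns mainly later transitions.

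The count is of couples. The rule groups participants, and the FAQ as listed rates only the person cared for, so the caregiving partner's own function is not scored even where the battery is used.

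**The case against.** The best defence is that the MoCA covers everyone at every interview, that Aim 1 is stratified by cognitive function, and that the sample size section favours continuous predictors such as the MoCA score. The screener also goes to everyone and asks whether the partner needs help with tasks, which gives some crude functional information. All of this stands. A reader might infer that group and decline are observed only where a partner takes the caregiver label. The documents do not support that: the cognitive component is fully observed. The screener item is not the FAQ, however, and no rule says that it may replace it.

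A reader might also conclude that the FAQ is certainly never obtained in normal couples. That is the likely consequence of the gated reading, but the all-participants wording prevents stating it as fact. If the FAQ is meant for everyone, Process and the screener text need correcting instead.

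Baseline groups might come from clinic diagnoses, or two normal MoCA scores might suffice for normal. The article states neither, and clinic diagnoses at entry would not supply the group at follow-up visits.

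It may seem natural to move the behaviour checklist and the continuity measure to a gate based on the partner's cognitive group. The documents give no firm ground for this. The caregiver gate is an openly stated design choice, and the continuity measure covers reactions to the caregiving role. Partners are also interviewed separately with the MoCA last, so the partner's current group may be unknown when the gate has to operate.

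**Conclusion.** The concern holds as an internal contradiction with a practical consequence. The Overview's rule cannot be applied as stated in couples without an FAQ, and on the clearest reading those are all couples without a self-identified caregiver. The loss is confined to the functional component. It matters most for separating MCI from ADRD and for recognising transitions.

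The size is uncertain. Across the assumed rates, 60 to 236 of 300 couples (20% to 79%) lack the FAQ at baseline, including 0 to 176 of the 240 MCI and ADRD dyads. Even the lower figure assumes that no partner in a normal dyad identifies as caregiver. No single percentage within this range can be defended from the documents.

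Selectivity is a plausible risk that rests on the Discussion's own remarks about who adopts the label. A reader might infer a demonstrated bias in the group comparisons, but the documents show neither its direction nor its size.

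The contradiction on relationship continuity is a minor, separate matter of wording.

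**What to change.** 1. Give the 10-item FAQ at every visit, with each partner as informant about the other, whatever the caregiver screener shows. Adapt its description, which now refers only to the person with dementia.
2. Reconcile Overview, Process and Assessment battery so that they agree on who completes the FAQ, and explain the asterisk.
3. State how a participant is grouped at a visit without an FAQ score, for example after the partner has left the study.
4. Keep caregiver self-identification as a variable for analysis. It should not decide whether function is measured.
5. In Process, describe relationship continuity as reported by the caregiver only.

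The behaviour checklist and the continuity measure can stay behind the caregiver screener.

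The cost is a few minutes per interview for a form already in the battery, and an edit to the skip logic. No new instrument or staff is needed. The change is worth making early, because function not recorded at a visit cannot be recovered in the analysis.
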